**Packaging and labelling**

The study team will repackage the powders into zip lock bags labelled only as the study arm A or B based on a local SOP that was written by the study team. The repackage process will take place at a clean room at School of Medicine, University of Nottingham, E-Floor by a food hygiene trained researcher. The researcher will use electronic food scale to weigh the powders. All prepared zip bags will be kept in a dry secure location. This will be in a locked cabinet in [name] and only accessible by designated study researchers. Participants will be provided the supplements mixed with the flavour in clear plastic food safe zip lock bags. Each bag will contain either 15g of pectin with 5g of cocoa powder and 15g of whey protein powder or 30g of whey protein powder with 5g of cocoa powder.

Participants will be advised to pour 250 ml of water into a shaker bottle, then empty the whole powder inside the bag and shake the bottle until they have consistent shake. They will be advised to add water up to 50 ml if required to enhance solubility. Participants will be advised to consume one bag per day, each participant will be given 42 zip bags to be consumed within 42 days. A brochure with easy instructions will be given to each participant.

Participants will be advised to take the intervention in the morning. If they forget to take it in the morning, they will be advised to take it once they remember. Moreover, participants will be advised to avoid missing doses or overdoses as much as they can and to report missing doses or overdoses incident to the study team if that will happen. They will be given a tracker to track their daily study supplement consumption.

The study team will use pectin that is provided from BOC SCIENCES INC, United States similar to the pectin that was used on the healthy volunteer study that was previously conducted at the University of Nottingham [31].

Mannitol 2.5% / Locust bean gum 0.2% will be used as an oral contrast during u scans. It will be an oral solution that will be prepared by the MRI research team on the MRI visit day. Each drink will contain 25g of Mannitol and 2g of Locust bean gum that will be dissolved in 1000 ml of water.

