**Storage, dispensing and return**

Pectin, whey protein, and cocoa powder are safe to be stored at room temperature. They will be kept in sealed containers in a dry location. This will be in a locked cabinet in [name] and only accessible by designated study researchers. Study Participants will be advised to bring back any unused zip bags and give them to the study team during follow up visits. Unused stock will be disposed as food waste into landfill waste.

Mannitol and Locust bean gum are safe to be stored at room temperature. They will be kept in sealed containers in a dry location. This will be in a locked cabinet in Sir Peter Mansfield Imaging Centre (SPMIC) and only accessible by the MRI research team. The contrast will be prepared and dispensed by the MRI research team.

Buscopan® will be stored at Sir Peter Mansfield Imaging Centre (SPMIC) and only accessible by the MRI research team. A qualified medical doctor, who will be a member of the research team too, will prescribe and dispense Buscopan® during the MRI visit.

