### Expected duration of participant participation

### Study participants will be participating in the study for 6 weeks, attending two 2 hours study visits. Participants who will agree to have MRI scans, including healthy volunteers, will need to attend two 4 hours MRI visits.

### Removal of participants from therapy or assessments/Participant Withdrawal

Participants may be withdrawn from the trial either at their own request or at the discretion of the Investigator due to safety reasons (including pregnancy) or development of severe adverse events, or due to failure to adhere to protocol requirements. The participants will be made aware that this will not affect their future care. Participants will be made aware (via the information sheet and consent form) that should they withdraw the data collected to date cannot be erased and may still be used in the final analysis. The research team will advise pregnant participants to stop the intervention and contact their GP if they have questions.

Study team will try their best to replace withdrawn participants.

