# TRIAL / STUDY INTERVENTION AND REGIMEN

Interested participants will be asked to contact the study team using the provided contact details on the advertisement poster or the study team will directly contact the potential participants if they are referred for recruitment by patient’s usual care team (which may include the investigator)at hepatology clinic via using encrypted emails (consent to share contact details will be documented in the patients notes) or those who have consented to contact for future research. The Participant Information Sheet (PIS) will be given to those expressing interest, either in person at NIHR Nottingham Clinical Research Facility at Nottingham University Hospitals NHS Trust, Queens Medical Centre or via royal mail or email. Study team contact information will be included in the PIS. Participants will have up to one week to decide whether they wish to take part or not. If a participant expresses interest after reading the PIS, they will be invited for a screening visit, which will be conducted in the NIHR Nottingham Clinical Research Facility at Nottingham University Hospitals NHS Trust, Queens Medical Centre by a trained member of the study team. During screening visit, the research team member will go through study details, allow the participant to ask any questions they have, and consider their decision. If they are willing to participate, they will be asked to provide consent and will be formally enrolled in the study. The research team member or member of the usual care team will then go through eligibility checklist with the participant to confirm their eligibility to participate in the study. If the medical notes are not available for participants to check their eligibility, then the chief investigator will rely on participants answers regarding their medications and medical conditions to confirm eligibility. A trained research Practitioner or nurse, who will be a member of research team at Nottingham University Hospital NHS Trust, will also perform CAP- FibroScan™ to measure liver fat and stiffness (if not completed in past month or not available in the medical note) and the result will be provided to the participant at the visit and will be documented in the medical notes. FibroScan™ results will be sent to the chief investigator to confirm eligibility.

FibroScan ™ is owned and maintained by Nottingham University Hospitals NHS Trust.

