**Baseline measures (visit 1):**

Participants will attend the visit fasted for at least 6 hours and provide the stool samples. Anthropometric measurements, including weight, height, waist/hip ratio and blood pressure, will be taken in duplicate by a trained researcher using standard procedures. A trained researcher will collect a blood sample (not more than 40ml) for analysis. Moreover, if participants consent to genetic testing, then blood sample for genetic analysis will be taken too. After randomisation, participants will receive their assigned pre-weighed supplement in food-grade pouches.

All the research activities at baseline visit will be done by [name] except blood and stool samples collection that will be done by a trained research practitioner or nurse, who will be a member of research team at Nottingham University Hospital NHS Trust.

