**Dietary intervention (6 weeks):**

Control and intervention arms: Each participant will be randomly assigned to either pectin with whey protein and cocoa powder or control whey protein with cocoa powder using online software (sealedenvelope.com) to determine intervention A or B at enrolment. Randomisation will ensure equal distribution of key characteristics that might confound between-group comparisons and will be evaluated using baseline data analysis. Participants in the intervention arm (N=15) will be required to take 15g of pectin combined with 15g of unflavoured whey protein powder and 5g of cocoa powder as a flavour per day for a period of 6 weeks. The participants in the placebo/control arm (N=15) will be required to take 30g of unflavoured whey protein powder combined with 5g of cocoa powder as a flavour per day for the same period of 6 weeks. All supplements will be provided, pre-weighed, in food grade pouches and will be given sufficient cover the total intake for the 6-weeks period. Participants will be asked to incorporate the supplement provided in 250-300ml of water taken once at morning or evening. Regular weekly contact will be made via phone calls by [name] to record patients’ feedback or any adverse event that might occur due to ingestion of supplements and to ensure participants receive any information that becomes available during the course of the research that may be relevant to their continued participation .

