**Follow-up/end of study measures (visit 2)**

At the end of 6 weeks, as for visit 1, stool samples and fasting blood samples (not more than 40ml), including blood sample for genetic analysis if the participants consented to that, will be collected, weight, height, waist/hip ratio and blood pressure measured, and FibroScan™ performed. The last visit will last no longer than 2 hours.

All the research activities at follow-up visit will be done by [name] except blood and stool samples collection and FibroScan™ that will be done by a trained research practitioner or nurse, who will be a member of research team at Nottingham University Hospital NHS Trust.

If the participant agrees to have MRI scans, then the study team will schedule a follow-up MRI scan as for MRI visit 1, taking around 4 hours.

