**Schedule of events**

|  | Screening | Visit 1 Baseline visit  (Day 1) | Visit 2 (6 weeks after visit 1) |
| --- | --- | --- | --- |
| Assessing participants eligibility and informed consent | X |  |  |
| Fasting blood sample collection |  | X | x |
| Faecal sample (collection by participant at home & brought to visit) |  | X | x |
| Anthropometric measurements (weight, height, waist/hip ratio and blood pressure) |  | X | x |
| CRF completion (demographics, health/med history) |  | x | x |
| Randomisation |  | X |  |
| Dietary supplementation Intervention start (dispense supplements and instruct) |  | x |  |
| FibroScan™ | x |  | x |
| MRI screening questionnaire (optional) |  | x | x |
| MRI (optional) |  | x | x |

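### The 42-bag supply covers the nominal visit 2 but not a late one: if the 5-day tolerance applies to visit 2, the primary sample can follow up to 4–5 full days without supplement

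*Protocol*

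**What the plan says.** **Supply.** Packaging and labelling sets one bag per day and states that "each participant will be given 42 zip bags to be consumed within 42 days". The section on the six-week dietary intervention sizes the supply the same way: participants "will be given sufficient cover the total intake for the 6-weeks period". Storage, dispensing and return adds that "Study Participants will be advised to bring back any unused zip bags". No section mentions spare bags, re-supply, or an instruction to keep dosing until visit 2.

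**Start.** The Schedule of events labels baseline as Day 1 and places randomisation, dispensing and the start of supplementation there. The baseline section agrees: "After randomisation, participants will receive their assigned pre-weighed supplement in food-grade pouches".

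**Visit 2.** The column heading in the Schedule of events begins "Visit 2 (6 weeks after visit 1". The follow-up section reads "At the end of 6 weeks, as for visit 1, stool samples and fasting blood samples". Blood is scheduled only at these two visits. The efficacy measure, described under Assessment of efficacy, is the change from baseline to follow-up compared between arms.

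**Tolerance.** Duration of the trial / study and participant involvement gives a participant duration of six weeks, plus or minus five days. It is the only tolerance on timing that the protocol states, and it is not tied by name to visit 2.

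**The concern.** The number of bags matches the nominal schedule exactly and leaves nothing over. If visit 2 may be up to five days late, the supply and the visit timing no longer fit. A participant who follows every instruction runs out of supplement and then gives the primary sample some days later.

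Visit 2 gives the only follow-up value for the inflammatory markers, so no earlier on-treatment sample can stand in for it. The Project Rationale attributes the expected benefit to fermentation of ingested pectin and to direct receptor binding, both of which depend on pectin being taken. Some loss of effect after stopping is therefore plausible, and it would pull the pectin arm towards the control arm. The optional MRI and the stool sample at follow-up would be affected in the same way. A late visit inside a permitted tolerance is not obviously a major protocol violation, so the per-protocol set might not remove it.

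**Working it through.** **Does the tolerance apply to visit 2?** Three points favour it.

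- It is the only tolerance given.
- Visit 2 is the last thing a participant does.
- Under Expected duration of participant participation, the six weeks are linked to the visits: "Study participants will be participating in the study for 6 weeks, attending two 2 hours study visits".

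One point goes the other way. At screening, before baseline, willing participants are told that "they will be asked to provide consent and will be formally enrolled in the study". A duration counted from enrolment could use the five days to absorb the interval from screening to baseline. The rest of the working takes the visit 2 reading as its condition.

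**Inputs.** Baseline is Day 1, visit 2 is six weeks later, the tolerance is 5 days, and 42 bags are taken at one per day. The first bag is taken on Day 1, or on Day 2 if the participant starts the next morning.

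**The plan's own figure.** 6 weeks × 7 days × 1 bag = 42 bags, which reproduces the stated supply.

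**Visit 2 days.** Nominal: 1 + 42 = Day 43. Earliest: 43 − 5 = Day 38. Latest: 43 + 5 = Day 48.

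**Last bag with full adherence.** First-bag day + 41: Day 42 (Day 1 start) or Day 43 (Day 2 start).

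**Full bag-free days before the sample.** Visit day − last-bag day − 1, not below zero:

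| Visit 2 on | Day 1 start | Day 2 start |
|---|---|---|
| Days 38–43 | 0 | 0 |
| Day 44 | 1 | 0 |
| Day 45 | 2 | 1 |
| Day 46 | 3 | 2 |
| Day 47 | 4 | 3 |
| Day 48 | 5 | 4 |

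At Day 48 the bag-free days are Days 43–47 (Day 1 start) or Days 44–47 (Day 2 start). Counted instead as days elapsed since the last bag, the figures are 48 − 42 = 6 and 48 − 43 = 5.

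**Sensitivity to the day count.** If the end of six weeks meant Day 42, the latest visit would be Day 47 and the largest gap 3–4 full days. The gap narrows but does not close.

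**Bags needed for daily dosing up to the day before visit 2.** Visit day − first-bag day. For Day 48 this is 47 (Day 1 start) or 46 (Day 2 start), so the present supply is 4–5 bags short.

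**Effect on the estimate.** The protocol gives neither a washout time for any marker nor an expected share of late visits. The dilution therefore cannot be calculated, and no figure is offered.

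**The case against.** The strongest reply is that the plan is consistent as written. Forty-two bags, a six-week intervention and a visit six weeks after baseline fit together with no bag-free day. The gap appears only when a tolerance stated for participant duration is carried over to visit 2. This stands, and it is why the point is conditional. A reader might infer that the supply figure itself is an error; the text does not support that. What it supports is an undefined tolerance which, on its likeliest reading, the supply does not cover.

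Second, the 4–5 days arise only on the last permitted day, and most of the range has no gap or a short one. This also stands. The same tolerance limits the gap for an adherent participant to 5 full days.

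Third, no harm is demonstrated. This is correct as far as size goes: nothing in the protocol shows that the markers revert within 4–5 days.

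Fourth, the daily tracker, the weekly calls and the return of unused bags make the last-bag date recoverable, and handling of late samples may be left to a statistical analysis plan. This answers the documentation side only. Knowing the date does not put the participant back on supplement, and leftover bags exist only for those who missed doses or attended early.

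**Conclusion.** The point holds as a conditional mismatch between supply and visit timing. If the five-day tolerance applies to visit 2, a fully adherent participant seen on Days 44–48 gives the only scheduled post-baseline primary sample after 0–1 (Day 44) up to 4–5 (Day 48) full bag-free days. It rests on three assumptions: the tolerance belongs to visit 2, baseline is Day 1 with the first bag on Day 1 or 2, and one bag is taken daily without omission.

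The likely direction is dilution of the pectin effect, with unknown size. Two stronger readings should be resisted. A reader might infer that the trial will measure a materially weakened effect; without washout data or a rate of late visits, the protocol does not show this. A reader might also suspect a spurious positive result. Supply and timing are the same in both arms, so there is no false-positive risk.

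The importance is low to moderate. It is a cheap improvement that keeps the primary sample on treatment.

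**What to change.** 1. In the study duration section and the Schedule of events, state that the tolerance of five days either way applies to visit 2.
2. Dispense 47 bags (5 spare), with the instruction to take one daily until the day before visit 2 and to return the rest. With 47 bags, a Day 48 visit has no bag-free day for either start day.
3. At visit 2, copy the last-bag date from the existing tracker into the case report form.

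**Cost.** For 30 participants, 30 × 5 = 150 extra bags, with a few more if withdrawn participants are replaced. The extra material is:

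- pectin: 15 × 5 × 15 g = 1,125 g
- whey: 15 × 5 × 15 g + 15 × 5 × 30 g = 3,375 g
- cocoa: 150 × 5 g = 750 g

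The case report form gains one field. The real downside is that total intake varies more with the visit date: 37–47 bags (Day 1 start) or 36–46 (Day 2 start), so 36–47 overall against 36–42 now. For late visits the intervention then runs a few days beyond the stated six weeks.

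**Not recommended.** Keeping 42 bags and cutting the late side of the tolerance (−5/+0) needs no extra supply, but a participant who cannot attend by Day 43 becomes a deviation or gives no follow-up sample. Without a post-baseline primary value that participant leaves the Full Analysis set. With 15 per arm, a sample taken a few days late is likely to be worth more than none.

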**Storage, dispensing and return**

Pectin, whey protein, and cocoa powder are safe to be stored at room temperature. They will be kept in sealed containers in a dry location. This will be in a locked cabinet in [name] and only accessible by designated study researchers. Study Participants will be advised to bring back any unused zip bags and give them to the study team during follow up visits. Unused stock will be disposed as food waste into landfill waste.

Mannitol and Locust bean gum are safe to be stored at room temperature. They will be kept in sealed containers in a dry location. This will be in a locked cabinet in Sir Peter Mansfield Imaging Centre (SPMIC) and only accessible by the MRI research team. The contrast will be prepared and dispensed by the MRI research team.

Buscopan® will be stored at Sir Peter Mansfield Imaging Centre (SPMIC) and only accessible by the MRI research team. A qualified medical doctor, who will be a member of the research team too, will prescribe and dispense Buscopan® during the MRI visit.

**Known Side Effects**

As this is a dietary intervention trial using widely available foodstuffs consumed as advised by manufacturers, no serious adverse events/side-effects or ethical issues are expected. Participants will be given the details of the trial supplements - those with food allergies or sensitivities to components of the foods/components will not be recruited. Increasing fibre intake may result in bloating amongst those who have a low habitual intake of dietary fibre. However, such effects are mild and not considered as a safety concern. Presence of inflammatory bowel disease, irritable bowel syndrome, and gastrointestinal resection surgery are exclusion criteria for the study to avoid exacerbating these conditions. Pregnant and breastfeeding women will be excluded from the study because there is limited data regarding the safety of pectin and whey protein consumption during pregnancy and breastfeeding.

The common side effect from administration of the Buscopan® (that will be used during MRI scans as antispasmodics) are very short lived (blurred vision and raised heart rate) and participants will be advised to stay at the test centre until their vision returns to normal (this normally occurs within 30 minutes of the injection). Rare side effects from administration of the Buscopan® injection include skin reactions, tachycardia, dry mouth, dyshidrosis, and in extremely rare cases angle-closure glaucoma. This will be monitored throughout the study visit at Sir Peter Mansfield Imaging Centre (SPMIC) by a registered medical doctor who will be a member of the research team and who will administer Buscopan® and monitor participants.

Mannitol 2.5% / Locust bean gum 0.2% will be used during MRI scans as oral contrast. Mannitol increases MRI contrast between the lumen and the bowel wall, and the addition of locust bean gum serves to counteract some of the recognised side effects associated with Mannitol ingestion, which can include flatulence and alteration of gastrointestinal microbiota leading to bowel spasms and diarrhoea.

# TRIAL / STUDY DESIGN

## TRIAL / STUDY CONFIGURATION

This a single centre placebo controlled randomised dietary intervention study in which participants will be grouped into the intervention (A) or placebo arm (B). Randomisation will be controlled for equal distribution of key characteristics (e.g. sex, ethnicity) that may confound between group comparisons and will be assessed by analysis of baseline data.

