| Description of interventions | Arm A: Pectin fibre (15g/day) combined with 15g whey protein supplement and 5g cocoa powder reconstituted as a shake Arm B (control/placebo): Whey protein supplement (30g/day) and 5g cocoa powder reconstituted as a shake.  To validate MRI scans as a tool to assess intestinal wall thickness to indicate gut permeability on MASLD patients, our team will scan 15 healthy volunteers twice, at baseline and after 6 weeks, and then compare their results with MASLD participant results at baseline and after 6 weeks. |
| Duration of study | Duration of the study:  24 months.  Duration per participant:  Each participant will participate for 6 weeks. |
| Randomisation and blinding | The study will be a parallel design, placebo-controlled, randomised dietary intervention study in which each participant will be randomly assigned to either pectin supplementation or control dietary supplement using online software (sealedenvelope.com). |
| Outcome measures | Primary outcomes:  Quantification of blood markers associated with physiological processes and pathways contributing to systemic inflammation pathway (TNFα, IL-6, IL-10, IFNᵞ, C-Reactive Protein, Zonulin (Haptoglobulin), IL-1β).  Secondary outcomes:   1. Assessment of changes in anthropometric measures 2. Assessment of changes in general metabolic indicators, such as fasting blood glucose and other blood-based markers relevant to MASLD (e.g., CK18-M30, CK18-M65, PROC3, Enhanced Liver Fibrosis (ELF), NIS2+™, YKL-40, microRNA miR-34a-5p, liver-associated enzymes such as Alanine Aminotransferase (ALT), Aspartate Aminotransferase (AST), gamma-glutamyl transferase (GGT), Alkaline Phosphatase (ALP)), bilirubin levels, lipid profiles, and platelet counts. 3. Exploration of modifications in non-invasive physiological assessments linked to liver characteristics, such as fat content and stiffness through controlled attenuation parameter (CAP) and transient elastography. 4. Observation of alteration in fat in liver and other surrounding abdominal organs through Dixon MRI sequence in patients who will agree to have 2 MRI scans. 5. Validation of MRI measures (T2*) as a tool to measure gut permeability among MASLD patients and investigation of changes in gut permeability in participants undergoing two MRI scans. 6. Investigation the presence of gene variants such as MUC2, encoding Mucin protein, that are associated with gut permeability. |

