## RANDOMIZATION AND BLINDING

The study will be a parallel design, placebo controlled, randomised intervention study in which participants will be allocated to either the intervention or placebo arm. The randomisation will be done through an online software (sealedenvelope.com) to determine intervention A or B at enrolment.

One of research team will be un-blinded and will be responsible for preparing and labelling of the intervention/placebo as either A or B based on random selection using an online software (sealedenvelope.com). A or B – pectin will be assigned to the arm in the first envelope. This information will be securely documented in a new sealed enveloped stored in the chief investigators locked desk. All other members of the team will be blinded to the assignment of A or B as the intervention.

This will be unblinded once the study is complete after the sample analysis and data analysis is complete.

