### Maintenance of randomisation codes and procedures for breaking code

The assignment of pectin as intervention A or B will be documented in a sealed envelope in the CI’s desk. This can be accessed and broken, if necessary, on direction of the CI in the event of any serious adverse event.

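### The protocol prints which letter is pectin although its blinding depends on hiding that, and one shared code means a single break discloses all 30 allocations to whoever is told

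*Protocol*

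**What the plan says.** Two parts of the protocol fix the meaning of the letters. The Synopsis, under Description of interventions, lists "Arm A: Pectin fibre (15g/day) combined with 15g whey protein supplement and 5g cocoa powder reconstituted as a shake" and "Arm B (control/placebo): Whey protein supplement (30g/day) and 5g cocoa powder reconstituted as a shake". Trial / Study Configuration repeats the link: "participants will be grouped into the intervention (A) or placebo arm (B".

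Two other parts treat the same link as a secret. Randomization and Blinding has one team member prepare and label the product, with pectin given to A or B by a random draw that is then sealed in an envelope in the chief investigator's locked desk. It adds: "All other members of the team will be blinded to the assignment of A or B as the intervention". Blinding is meant to last until the sample and data analyses are finished. The section on maintaining and breaking the code says that the envelope records whether pectin is A or B, and continues: "This can be accessed and broken, if necessary, on direction of the CI in the event of any serious adverse event".

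The letters are also the working labels. The online software is used "to determine intervention A or B at enrolment", and Packaging and labelling says that the bags are "labelled only as the study arm A or B". No participant-level or kit number for the bags, and no individual code-break record, is described.

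**The concern.** The blinding has a single safeguard: nobody but the preparer knows which letter is pectin. The protocol appears to give that fact away in two places, using the letters that staff will see on the bags. Even if the printed letters were removed, every participant in an arm would carry the same letter, so one disclosure about one participant would decode the whole trial for the person who receives it.

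The people exposed are those whose judgement the blinding should protect. Trial/Study Management gives one student the visits, the sample analysis and the data analysis. The chief investigator determines seriousness and causality of serious adverse events and has discretion over whether a participant with a severe reaction is advised to continue or withdraw. Weekly calls collect feedback and adverse events. Membership of the per-protocol set rests on a judgement about major violations. Knowledge of the arm, or a mistaken belief about it, could colour each of these. The assayed biomarkers that form the primary endpoint are less open to such influence than reported symptoms, but their handling and analysis remain with staff who can see the letter.

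**Working it through.** The protocol gives no figure on this point, so the check is a comparison of sections followed by a count.

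**Step 1: where each letter appears**

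| Section | What it says about A and B |
| --- | --- |
| Synopsis, Description of interventions | A is pectin, B is whey control |
| Trial / Study Configuration | A is intervention, B is placebo |
| Randomization and Blinding | Which letter is pectin is drawn and concealed from all but one member |
| Maintenance of randomisation codes | One envelope holds that fact |
| Randomization and Blinding; Dietary intervention | Software returns A or B for each participant |
| Packaging and labelling | The bag shows only A or B |

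**Step 2: the possible readings**

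- The draw makes A pectin. The printed text is then true, and anyone with the protocol who sees a bag knows that participant's arm.
- The draw makes B pectin. The Synopsis and Trial / Study Configuration are then false, and a staff member who relies on them is wrong about every randomised participant.
- The letters in the Synopsis and Trial / Study Configuration are generic arm names, unconnected with the bag letters. The protocol never says so and uses identical letters for design arm, randomisation output and bag label.

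All three readings leave text that has to be corrected.

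**Step 3: what one code break discloses**

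Inputs, from Dietary intervention: 15 participants in the intervention arm and 15 in the control arm.

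- Randomised participants: 15 + 15 = 30.
- As written, the envelope holds one two-way fact. Combined with the visible letters it decodes 30 of 30 allocations (100%) once all are randomised. If it is opened earlier, it decodes those allocated so far and every later letter as it is issued.
- With a unique code and a separate record per participant, one break decodes 1 of 30, that is 1/30 = 3.3%.

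The 15 healthy volunteers scanned by MRI are not randomised and do not enter the count.

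**Step 4: size of the relabelling task**

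Packaging and labelling gives 42 bags per participant: 30 x 42 = 1,260 bags. Each replacement for a withdrawn participant would add 42.

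**The case against.** The best defence is that Randomization and Blinding is the section that governs. Staff who read it know that the letter was drawn, and may discount the letters printed elsewhere as design shorthand. That is a fair reading of intent, and it is why one cannot say that staff will certainly know the arm. It does not remove the contradiction, because nothing in the text separates the two uses of the letters.

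A reader might infer that the trial therefore has no blinding. The documents do not support that. Nothing shows that participants receive the Synopsis or the design section; they are promised details of the supplements, not the code. The Sample Labelling section lists trial code, initials and date of birth, with no arm letter, and some assays may go to contracted laboratories.

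A reader might also infer that any code break unblinds everyone. It informs whoever opens the envelope or is told. Other staff and the participants stay blind, and opening is conditional on need and on the chief investigator's direction. The protocol expects no serious adverse events from the supplements, so a break may never happen. These points limit how likely the exposure is and how many people share it, but the number of allocations revealed to each person told is unchanged.

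Finally, one might infer that staff who see the letters can predict coming allocations and enrol selectively. The protocol does not state that blocks are used. It speaks only of control for characteristics such as sex and ethnicity, which could mean stratification or minimisation. Eligibility is settled at screening, before randomisation at visit 1. No predictability claim or figure can be drawn from this text.

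**Conclusion.** The point holds in two parts of unequal weight.

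First, the protocol contradicts itself on the one fact that its blinding depends on. Staff who hold the protocol and see the bags would know, or wrongly believe that they know, each participant's arm. This must be reconciled before supplements are dispensed, because letters already seen cannot be concealed again.

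Second, the shared letter and single envelope are a real but lesser design weakness that would survive a wording correction. One permitted break discloses all 30 randomised allocations to each person told, where individual records would disclose one.

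The conclusion assumes that the unblinded preparer, whom the protocol does not identify, is neither the student nor the chief investigator. It also assumes that the weekly caller, whose name is removed from the public text, is the student. If the caller is someone else, that person simply joins the staff exposed.

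**What to change.** - In the Synopsis and Trial / Study Configuration, replace the letters with neutral names such as pectin arm and control arm.
- Before dispensing starts, label each participant's bags with a unique participant or kit number instead of A or B.
- Have the preparer who is already unblinded hold the list linking numbers to treatment, with a separate code-break record for each participant.
- Rewrite Packaging and labelling, Randomization and Blinding, and the section on maintaining and breaking the code to match, and bring the A/B wording under Dietary intervention into line.

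The cost is modest but not zero. About 1,260 bags need coded labels. Supplements are handed over after randomisation at visit 1, which ready-made A and B stock makes simple. With numbered packs, the randomisation system must return a pack number, or the preparer must supply the numbered pack at that visit. No new role is needed, since the protocol already provides an unblinded preparer, and no dose or clinical rule changes.
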